#### 9.4.3 SAFETY ANALYSES

We will detail all treatment-related severe AEs and SAEs experienced by the child-caregiver dyads. The DCOC will present summary statistics for the study overall and by individual site.

---

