## 8.2 SAFETY AND OTHER ASSESSMENTS

Because this study is of an educational intervention, study-related adverse events (AEs) and serious adverse events (SAEs) are not expected. Given the minimal risk of the study, the study team will not solicit AEs or SAEs. However, the study team will provide all participants with a phone number to report AEs and SAEs.

The study team will track severe AEs and SAEs that are potentially study related.

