#### 8.3.3.2 RELATIONSHIP TO STUDY INTERVENTION

All severe AEs and SAEs must have their relationship to the trial intervention assessed by the site PI or a qualified clinician, who examines and evaluates the participant based on temporal relationship and their clinical judgment. We will grade the degree of certainty about causality by using the categories below.

**Related.** We know the AE occurred with the trial intervention, there is a reasonable possibility that the trial intervention caused the AE, or there is a temporal relationship between the trial intervention and the AE. Reasonable possibility means that there is evidence to suggest a causal relationship between the trial intervention and the AE.

**Not Related.** There is not a reasonable possibility that the administration of the trial intervention caused the event, there is no temporal relationship between the trial intervention and event onset, or there is an established, alternate etiology.

---

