#### 8.3.4 TIME PERIOD AND FREQUENCY FOR EVENT ASSESSMENT AND FOLLOW -UP

The study team will provide participants with a telephone number to report severe AEs or SAEs.

Because this minimal-risk study is for an educational intervention, the study will not actively solicit AEs or SAEs. When a site coordinator or site PI learn of a severe AE or SAE, they will refer participants to their primary care physician. The site coordinator will record the severe AE or SAE in the appropriate EDC system and track it.

The site coordinator will record severe AEs, as described in the next section and in the MOP. Severe AE data collection typically includes event description, time of onset, if available, resolution time and day, if available, and operational PI's assessment of severity, relationship to study participation or intervention (assessed only by those with the training and authority to make a diagnosis), and time of resolution/stabilization of the event. The site coordinator must appropriately document severe AEs occurring during the trial, regardless of relationship to the trial. The DCOC safety personnel will track severe AEs until one of the following criteria are met: resolution, the condition stabilizes, the event is otherwise explained or is judged by the site investigator to be no longer clinically significant, or the participant is withdrawn from the study. DCOC safety personnel will follow all SAEs by asking about the SAE every 14 days until resolution or until the site investigator determines the event to be chronic, or until the participant is stable. The DCOC may request other supporting documentation of the event and should be provided as soon as possible.

Site coordinator will document changes in a severe AE in the source document and EDC to allow an assessment of the duration of the event. Severe AEs characterized as intermittent require documentation of onset and duration of each episode.

Participants may report severe AEs for 7 days after completing study procedures and SAEs for 30 days after completing study procedures. Site coordinators and/or DCOC safety personnel will record and track according to this protocol and DCOC standard operating procedures (SOPs).

---

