#### 8.3.5 ADVERSE EVENT REPORTING

Site coordinators or the study team will record severe AEs in the EDC system, include them in the statistical analysis, and follow the reporting procedures outlined in the study-specific MOP. The MOP section on reporting severe AEs will encompass the requirements of:

1. The cIRB's policies and procedures,
2. SOPs for the Streamlined, Multisite, Accelerated Resources for Trials IRB Reliance platform (SMART IRB),

3. ICH E6(R2), Good Clinical Practice: Integrated Addendum to ICH E6(R1): Guidance for Industry, and
4. The local IRB's policies and procedures, when applicable.

If there are discrepancies between the procedures, we will follow the most stringent of the requirements.

If this study is deemed to be greater than minimal risk, or the cIRB otherwise requires a continuing review report, the DCOC will report severe AEs to the cIRB at the time the continuing review is submitted. The DCOC will report to the cIRB at UAMS, as specified in the study-specific IRB communication plan, which is based on recommendations of SMART IRB. Sites will also report severe AEs to the local IRB, per local IRB policies and procedures, and make them available to the sponsor (the DCOC) on a continuing basis through the EDC system. We will report to the DSMB, per the DSMB charter.

The study-specific MOP will describe the details of the reporting structure and additional details related to timelines for reporting.

---

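### Section 9.4.3 sets a narrower safety scope than 8.3.4 and 8.3.5, and filters on a relatedness classification whose two categories overlap

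*Protocol*

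**What the plan says.** Four sections of the protocol describe which safety events count, and they do not agree.

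- **9.4.3 (Safety Analyses):** "We will detail all treatment-related severe AEs and SAEs experienced by the child-caregiver dyads". A second sentence promises summary statistics for the whole study and for each site, without saying which events they cover.
- **8.3.5 (Adverse Event Reporting):** "Site coordinators or the study team will record severe AEs in the EDC system, include them in the statistical analysis". No relatedness condition is attached.
- **8.3.4 (Time Period and Frequency):** "The site coordinator must appropriately document severe AEs occurring during the trial, regardless of relationship to the trial". The same section says that events are not actively solicited, so this covers events that reach the sites' attention.
- **8.2 (Safety and Other Assessments):** "The study team will track severe AEs and SAEs that are potentially study related".

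Relationship is defined in 8.3.3.2, where the site PI or a qualified clinician assesses every severe AE and SAE. The last condition that makes an event Related reads "or there is a temporal relationship between the trial intervention and the AE". The last condition that makes it Not Related reads "or there is an established, alternate etiology".

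**The concern.** Two defects meet in one short section.

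First, the scope is stated in three ways. A statistician who follows 8.3.5 would tabulate every recorded severe AE. One who follows 9.4.3 could detail only those judged related. Both could claim to have followed the protocol.

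Second, the qualifier in 9.4.3 depends on a two-category classification whose categories are not exclusive. The events that 8.3.3.3 names as possible are mostly respiratory infections, gastroenteritis and other common infections. These often have an identifiable cause of their own. In infants attending up to four well-child visits in 12 months, some will fall close to a visit. Such an event, if severe, fits both categories, and two sites could code the same event differently.

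What is at stake is whether the safety table means the same thing at both sites. The study has one arm and no blinding, so there is no control-group rate to offset a relatedness judgement made by staff who know that the intervention was delivered.

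**Working it through.** The protocol states no safety figure to reproduce. The check sets the sections side by side and then tests the definitions logically.

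**Step 1. Scope.**

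| Section | Activity | Events covered |
|---|---|---|
| 8.2 | Tracking | Severe AEs and SAEs, potentially study related |
| 8.3.4 | Documentation | Severe AEs, any relationship |
| 8.3.5 | Recording and statistical analysis | Severe AEs, no relatedness condition |
| 9.4.3 | Detailing in the safety analysis | Treatment-related severe AEs, and SAEs |

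The direct conflict on analysis is between 8.3.5 and 9.4.3. Section 8.3.4 concerns documentation, not analysis. It matters because it shows that unrelated severe AEs will be in the database. Section 8.2 conflicts with 8.3.4 on which events are followed.

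**Step 2. Relatedness.** Take three yes/no facts from 8.3.3.2: R, a reasonable possibility of causation; T, a temporal relationship; A, an established other cause. The conditions within each definition are joined by *or*, so read literally:

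- Related = R or T
- Not Related = (not R) or (not T) or A

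The further Related condition, that the event is known to have occurred with the intervention, is left out. Including it could only widen Related.

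| R | T | A | Related | Not Related | Result |
|---|---|---|---|---|---|
| no | no | no | no | yes | Not Related only |
| no | no | yes | no | yes | Not Related only |
| no | yes | no | yes | yes | both |
| no | yes | yes | yes | yes | both |
| yes | no | no | yes | yes | both |
| yes | no | yes | yes | yes | both |
| yes | yes | no | yes | no | Related only |
| yes | yes | yes | yes | yes | both |

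Five of the eight combinations meet both definitions, one is Related only and two are Not Related only. If the two rows with R but no T are set aside as unlikely in practice, 5 − 2 = 3 of 8 − 2 = 6 still meet both. These are counts of logical cases, not of expected events. Section 8.3.3.2 gives no rule for which category prevails.

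**The case against.** A reader might infer that 9.4.3 reports related events only, so that other collected events would go unreported. The text does not support that. Section 9.4.3 never says only. Its adjective may attach to severe AEs and not to SAEs, and its second sentence carries no filter. Elsewhere, 8.3.5 includes recorded severe AEs in the analysis and provides for DSMB reporting under the charter. Section 8.3.6 has SAE data summarised for the central IRB, 9.4.1 promises presentation of all study data, and 9.4.7 provides de-identified data for all participants. This objection stands: the defect is an inconsistent statement of scope, not suppression of events.

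It can also be said that classification is not arbitrary. Section 8.3.3.2 requires clinical judgement, and most clinicians would probably treat an established other cause as decisive. That is fair, and dependent on the assessor is the accurate description. Judgement does not, however, make two overlapping definitions exclusive.

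A table full of routine infant illness is not a likely result either, because 8.3.1 limits AE recording to severe events.

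Finally, table layout by relationship commonly belongs in the SAP, which is not at hand, so the missing column alone is no error. But a SAP cannot satisfy both 8.3.5 and a restrictive reading of 9.4.3, and it cannot repair definitions that sites apply when they classify events.

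**Conclusion.** The point holds as a contradiction in scope together with a classification rule that does not separate its two categories. The second part rests on reading the *or* wording of 8.3.3.2 literally, and the protocol supplies no other reading.

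The size is modest. This is a minimal-risk educational pilot with no comparative safety test, and neither the primary endpoint nor the sample size is touched. A reader might want to say how many events would move in or out of the table. The protocol gives no event rate, so no such number can be derived. Applying an assumed one-year rate to all 86 infants would also be wrong, because dyads above the baseline LENA cutoff leave after Phase 1. The goal is at least 66 dyads in Phase 2, with 53 expected to complete. Nor would every event hinge on the reading, since three of the eight combinations fall in one category only.

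**What to change.** 1. State one scope consistently in 8.2, 8.3.4, 8.3.5 and 9.4.3.
2. In 9.4.3, report all recorded severe AEs and SAEs by relationship to the intervention, overall and by site. This agrees with 8.3.5. Say that recorded means events that came to the sites' attention, since events are not solicited.
3. Reword 8.3.3.2 so that Related and Not Related are mutually exclusive, with a stated rule for an event that has both a temporal link and an established other cause.

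The cost is protocol wording and one table column. Events that reach the sites are already recorded, and 8.3.3.2 already requires a relationship assessment for each severe AE and SAE. If any events have been classified under the present wording, they should be checked against the revised definitions.

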#### 9.4.4 BASELINE DESCRIPTIVE STATISTICS

Baseline characteristics will be summarized using the descriptive statistics specified in **Section 9.4.1**.

---

#### 9.4.5 PLANNED INTERIM ANALYSES

None.

---

#### 9.4.6 SUB-GROUP ANALYSES

None.

---

#### 9.4.7 TABULATION OF INDIVIDUAL PARTICIPANT DATA

The statistical team will provide a description of participants in counts and percentages, including the creation of a Consolidated Standards of Reporting Trials (CONSORT) diagram. De-identified data will also be provided for all study participants.

---

#### 9.4.8 EXPLORATORY ANALYSES

We will examine barriers to enrollment, including our ability to contact caregivers, the proportion of caregivers that consent to participate in the study, enrollment of caregiver-child dyads, and caregivers' willingness to

complete baseline assessments. We will also examine characteristics related to attrition for caregiver and provider participants. Descriptive statistics will be used in these exploratory analyses.

Caregiver language promotion behaviors (LENA) will be examined and reported descriptively. Child vocalization scores (LENA) will be reported descriptively. We will also examine associations of differences in change in LENA scores with caregiver characteristics (e.g., low, or high baseline LENA scores, education level, SES) using analysis of variance (ANOVA) models or linear regression models.

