The pre-post intervention design allows us to evaluate participant completion of critical measures that will be used in the future, large-scale RCT. Importantly, it also allows us to estimate expected change in caregiver language-promotion skills in response to the intervention. Since TWMB targets caregiver language behaviors, the design includes a pre-post intervention assessment of the HLE using LENA audio-recordings, which is an objective assessment and the research standard for measuring talk with children. These recordings will come from a small recorder (“talk pedometer”) children wear (in a shirt pocket) for a day at a time. See Section 8.1.2 for details about LENA assessment.

In line with emerging guidance on pilot studies prior to high-quality large-scale efficacy trials, the current study design does not include a control group. This is due to the high likelihood of an underpowered sample in this pilot to detect meaningful differences in the endpoints that will be evaluated in the large-scale RCT. By focusing the pilot on delivering TWMB in both clinics, we can maximize the number of dyads ( $n = 86$ , with goal of having at least 66 dyads able to enter phase II) to obtain a better estimate of variability in intervention response, rather than using resources to conduct underpowered difference tests between conditions for an untested intervention in this setting.

Site study teams will consent dyads and will complete baseline measures prior to the start of TWMB implementation in clinics (or prior to having a WCC visit with TWMB during the intervention period). To gather preliminary evidence that TWMB is effective for families with an inadequate HLE and to avoid ceiling effects in this small sample, we will enroll dyads with baseline LENA scores that are  $\leq 75^{\text{th}}$  percentile compared to age-referenced normative data. Of note, previous data have shown that without intervention, caregiver’s language-promotion behaviors do not show significant change across birth to 48 months of age. Therefore, evidence of change in caregiver’s language-promotion behaviors over the course of the TWMB pilot trial would be meaningful preliminary evidence of TWMB efficacy for the home language environment.

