### 5.1.2 CAREGIVER-CHILD PARTICIPANT INCLUSION CRITERIA

For this study, each child-caregiver dyad will consist of:

1. A caregiver who will receive TWMB during routine WCC visits for their child at participating clinics, and
2. The child of the above caregiver for whom the WCC visits are conducted.

A potential caregiver participant must meet all the following inclusion criteria to enroll in the study:

1. Be the age of majority, or older, as defined by the state of residency.
2. Able to complete study measures in English.
3. Have the legal authority to consent to participate for themselves and to consent on behalf of their child.

To proceed to the follow-up portion of the study the caregiver (dyad) must have a LENA baseline assessment score that is  $\leq 75^{\text{th}}$  percentile compared to a child's age-referenced normative data.

A potential child participant must meet all the following inclusion criteria to be enrolled in the study:

1. Receive WCC at a participating clinic from a participating provider.
2. Be zero to nine months (+ 0–30 days) old at enrollment.
3. Was born at full term ( $> 37$  weeks gestation).
4. Was born in a singleton birth (i.e., was the only child delivered during the birth).

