**Figure 7. LENA “Talk Pedometer” Recorder and Vest With Instructions**

[figure not shown]

LENA is the research standard for measuring talk with children because it is user-friendly and widely used in the field to successfully collect data from families of diverse characteristics. Since the technology became available in 2008, LENA data have been published in 150+ observational and interventional studies involving many hundreds of children. LENA is family-friendly and has been used successfully in many large-scale studies with infants and toddlers using the methods we will use.

Study staff will mail the LENA recorder and vest to the family; alternatively, the LENA recorder may be provided to the family at a clinic visit. Study staff will then complete a short phone call with the family to walk through how to use the device and answer any questions (simple instructions are also provided with the device, see **Figure 7**). If the family opts for electronic communications, the family will get an electronic link and be able to complete the review and questionnaire electronically. Families will be asked to complete 2 day-long recordings during a period when the child is in the home setting (i.e., not at daycare), turning on and putting on the device at the start of the day when the child first wakes up and leaving it on for 12-16 hours. The LENA recorder can remain turned on and be taken off and left nearby during bath or naps, if needed. The device automatically turns off when the maximum recording time is reached. Families will be asked where the recording was obtained. Families will complete a recording on two separate days during Baseline (i.e., Phase 1); Phase 2 participants will complete a recording on two separate days again during the Post-Intervention Assessment phase.

Participants will be asked to complete questionnaires at the end of each recording day. These questionnaires will ask about where the child was (based on 2-hour intervals) during the recording time period, what the child was doing, and who was with the child during the recording time period. A paper version of the question will be sent with the LENA device. The adult participant will have the option to answer the questions electronically, by phone, or by sending the completed paper questionnaires back with the LENA devices (see below).

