### 9.2 SAMPLE SIZE DETERMINATION

The primary endpoint is a binary variable of reaching at least a 10% increase in AWC or CTC percentile scores from Baseline (Week 1) to Post-intervention (Week 48). This increase is based on previous language-promotion intervention studies using LENA, which reported statistically significant gains (for intervention versus control) for parent language-promotion behaviors ranging from 10-30%. In terms of clinical relevance, the proposed 10% gain in AWC would be an increase of ~160 adult words per hour, which equates to an increase of ~3 points in child language standard scores on the Bayley Scales of Infant Development and the Preschool Language Scale (proposed two-point increase for every increase of 100 adult words per hour for children age birth to four years-old).

The study is expected to have at least 70% of caregiver participants reaching improvement in language-promotion behaviors at the end of the study. In other words, the targeted rate of improvement in language-promotion behaviors is 70%. We plan a total accrual of up to 86 child-caregiver dyad participants into the study with a goal of having at least 66 dyads enter into phase II of the study. With an estimated phase II attrition rate of 20%, we expect that a total of 53 enrolled child-caregiver dyad participants will complete phase II of the study and hence the effective sample size is 53. Using a two-sided exact test with a significance level of 0.05, we are able to reach 85% power to reject a null rate of improvement at 50%, should the targeted rate of improvement be reached.

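### Section 9.4.8 tests change in LENA score against low or high baseline LENA with no control group, so regression to the mean alone will tend to make low-baseline families appear to gain more

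*Protocol*

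**What the plan says.** Section 9.4.8 (Exploratory Analyses) of the protocol will examine "associations of differences in change in LENA scores with caregiver characteristics (e.g., low, or high baseline LENA scores, education level, SES"). Low or high baseline LENA is the first characteristic named. The method is stated as "using analysis of variance (ANOVA) models or linear regression models".

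Four other statements bear on how that analysis behaves:

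- Section 4.2.1: "the current study design does not include a control group". The design is a single-arm pre-post comparison.
- Section 5.1.2: "To proceed to the follow-up portion of the study the caregiver (dyad) must have a LENA baseline assessment score that is" at or below the 75th percentile of the age norms. Follow-up is therefore selected on the same variable that serves as predictor.
- Section 8.1.2: "Families will complete a recording on two separate days during Baseline", and Phase 2 dyads do so again at Week 48. One usable day of the two counts as complete at Week 48.
- Section 9.2: "we expect that a total of 53 enrolled child-caregiver dyad participants will complete phase II of the study".

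The protocol does not mention regression to the mean, measurement error or a retest correlation. Section 9.4.1 leaves the detail of the outlined analyses to a separate SAP, which was not available for this review.

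**The concern.** Change is the Week 48 score minus the baseline score. A dyad whose baseline days happened to be quiet scores low at baseline and, on average, higher later. A dyad whose days happened to be talkative does the reverse. Regressing change on baseline, or comparing low and high baseline groups on change, picks up this pattern whether or not the intervention works.

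Section 4.2.1 relies on earlier data showing that without intervention caregiver behaviors "do not show significant change across birth to 48 months of age". That concerns the average. A stable group mean is fully compatible with individual dyads moving toward it from both sides.

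The pilot exists to prepare a randomized trial, and section 4.2.1 gives a better estimate of variability in response as a reason for forgoing a control arm. A spurious finding that the lowest-scoring families respond best would distort exactly that information.

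**Working it through.** The protocol states no figure for this analysis, so there is none to reproduce.

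**Inputs**

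- Completers: 66 dyads entering Phase 2 with 20% attrition (section 9.2), 66 × 0.80 = 52.8, about 53.
- Selection: baseline at or below the 75th percentile (section 5.1.2), a cut at z = 0.674.
- Intervention effect: none, and no change in the mean.
- Retest correlation r between baseline and Week 48: not in the documents. Assumed 0.5 to 0.9.
- Two-sided 0.05 for the exploratory test: assumed, since section 9.4.8 sets no level.

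**Step 1: slope.** Let b be baseline and p the Week 48 score, with equal SD σ and correlation r. Then Cov(p − b, b) = rσ² − σ² and Var(b) = σ², so the slope of change on baseline is r − 1. Selection on b does not alter this slope when the relation is linear.

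**Step 2: correlation after the cut.** For a standard normal cut above at c = 0.674, φ(c)/0.75 = 0.318/0.75 = 0.424. The remaining variance is V = 1 − 0.674 × 0.424 − 0.424² = 0.535. The correlation of change with baseline is −(1 − r)√V / √[(1 − r)²V + 1 − r²]. At r = 0.5 this is −0.366/0.940 = −0.389.

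**Step 3: chance of p<0.05.** By Fisher's z, this is Φ(√(53 − 3) × atanh|correlation| − 1.96). At r = 0.5: 7.07 × 0.411 = 2.90, and Φ(0.94) = 0.83.

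| Assumed r | Slope | Correlation | p<0.05, formula | p<0.05, simulation |
|---|---|---|---|---|
| 0.5 | −0.50 | −0.39 | 83% | 84% |
| 0.7 | −0.30 | −0.29 | 57% | 58% |
| 0.8 | −0.20 | −0.24 | 40% | 40% |
| 0.9 | −0.10 | −0.17 | 22% | 22% |

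**Step 4: percentile scale.** The endpoint uses percentile scores, so the no-effect case was also simulated on that scale (4,000 trials per r, same cut, n = 53). The lower and upper halves are split at the median baseline.

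| Assumed r | p<0.05, regression | p<0.05, low/high ANOVA | Mean change, lower half | Mean change, upper half |
|---|---|---|---|---|
| 0.5 | 91% | 79% | +16.4 points | −3.8 points |
| 0.7 | 65% | 54% | +10.2 | −2.6 |
| 0.8 | 45% | 39% | +7.0 | −2.0 |
| 0.9 | 22% | 21% | +3.6 | −1.0 |

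At r = 0.95 the regression still rejects in 11% of trials. If every dyad truly gains the same 0.3 SD, the lower half still appears to gain more (18.7 against 6.9 points at r = 0.7).

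**Step 5: education and SES.** With no effect, the 75th-percentile cut and SES correlated 0.4 with the true score (an assumption), the slope of unadjusted change on SES is +0.02 to +0.07, with p<0.05 in 7% to 8% of trials. That is small and opposite in sign to the baseline artefact.

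**Step 6: ANCOVA.** Regressing p on b gives slope β; regressing p − b on b gives β − 1. They are the same estimate shifted by 1, so ANCOVA adds nothing on the baseline question. In the setting of step 5, adjusting for the error-prone baseline produces an SES coefficient of +0.04 to +0.15 and p<0.05 in 11% to 22% of trials.

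**Step 7: splitting the baseline days.** Day 1 selects and classifies; day 2 is the baseline for change. With stable true scores and independent day-to-day noise, at single-day reliability 0.5, 0.7 and 0.8 the regression false-positive rate falls from 71%, 42% and 24% to 6.7%, 6.0% and 5.0%.

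**The case against.** The strongest reply is that the protocol commits to very little here. It is one sentence in an exploratory section, with characteristics given as examples, no hypothesis, no significance level and no statement of whether predictors enter singly or jointly. The SAP is to supply the detail. The primary responder analysis does not depend on it. Section 4.2.1 already says the future trial will have a control arm and no LENA cutoff, and no document says this result will decide that trial's design.

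Most of that stands and limits the consequence. It does not remove the point. Baseline LENA is named as a predictor of change in the protocol itself, both model families named share the flaw, and entering other predictors jointly does not mend the baseline coefficient.

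A reader might infer that education and SES inherit the same artefact because they track the home language environment. The documents do not support this. Regression to the mean comes from error in the baseline measurement, and SES relates to the true score, not to that error. Without the entry cut the expected slope on SES is zero; with it, step 5 shows only a slight bias in the other direction.

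A reader might also infer that the analysis would favour low-scoring families whatever the truth. That is too strong. A real effect larger in high-baseline families would offset the artefact, and whether the result reaches significance depends on a retest correlation the documents do not give.

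**Conclusion.** The point holds for the baseline-LENA predictor and for that predictor only. With no intervention effect, the expected slope of change on baseline is about r − 1. For r assumed between 0.5 and 0.9, a regression tested against zero gives p<0.05 in about 84% down to 22% of trials, against a nominal 5%. The direction, in expectation, needs only r below 1 and similar spread at the two time points. The size rests on the assumed r, approximate normality, the 75th-percentile cut and 53 completers. Nothing in a single-arm design can separate this pattern from differential response. It is worth correcting because the analysis is named and the correction is nearly free, but it does not affect the primary result.

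**What to change.** Remove baseline LENA as a tested predictor of change in section 9.4.8, and carry that into the SAP. Two alternatives are acceptable:

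- Report change by baseline level descriptively only, with an explicit statement that regression to the mean is expected to produce larger gains at low baseline.
- Use one usable baseline day to classify dyads and the other as the baseline for change. The figures in step 7 assume that the classifying day also determines entry to Phase 2. The split does not remove true drift over 48 weeks.

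If a slope is reported, compare it with the slope expected from retest reliability, not with zero. State that reliability estimated from the two baseline days ignores true drift over 48 weeks and so under-corrects.

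Do not replace the analysis with ANCOVA for this purpose, for the reasons in step 6. Education and SES can remain as predictors of unadjusted change. Leave the question of who responds best to the controlled trial.

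The cost is one exploratory test or, if days are split, the dyads without two usable baseline days. No new data are needed.
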